## **4 OBJECTIVES**

The overall goal of our research project is to increase the availability to evidence-based psychological treatments of adolescent MDD.

### **4.1 PRIMARY AND SECONDARY OBJECTIVES**

#### **Primary:**

1. To determine the clinical efficacy of Guided and Self-guided I-BA for depression for reducing depressive symptom severity (as measured by the CDRS-R (27) in adolescents with mild and moderate MDD, compared with an active control intervention (treatment as usual within primary or secondary child and adolescent mental health care). The primary endpoint is the follow-up 3 months post-treatment.

#### **Secondary:**

1. To establish the 12-month durability of the treatment effects.
2. To conduct a health-economic evaluation of guided I-BA for depression and self-guided I-BA for depression, compared with TAU, from multiple perspectives, both in the short term (primary endpoint) and the long term (12-month follow-up).

#### **Research questions:**

1. Is guided and self-guided I-BA more efficacious than TAU in regard to reduction of depressive symptoms?
2. Is guided and self-guided I-BA more cost-effective than TAU?
3. Is self-guided I-BA more cost-effective than guided I-BA?
4. Are the therapeutic gains of I-BA maintained long term (i.e., 1 year after the intervention)?

## **5 PROJECT DESCRIPTION**

### **5.1 DESIGN**

This will be a single site randomised controlled trial with national recruitment that will include 215 adolescents with mild to moderate depression. Participants will be randomised to receive 10 weeks of either (1) guided I-BA or (2) self-guided I-BA or (3) treatment as usual (TAU), at a ratio of 1:1:1 (72 in each group). TAU will be provided by regular mental health care clinics, within either primary or secondary care.

## 5.2 CONTROL GROUP JUSTIFICATION

The choice of type of control condition in a trial for a psychological intervention depends on several factors including the disease and its characteristics, the development phase, the purpose of the study, and the resources available (28). We decided on treatment as usual for the following reasons. (1) We are interested in comparing I-B to TAU, to see if it is less, equally or more effective than TAU. We are also interested in evaluating if it is cost-effective compared to TAU. (2) We consider depression (mild to moderate) to be associated with an intermediate patient risk and that contact with health care is necessary to ensure patient safety. (3) Waitlist would not be the most ethical choice since there are more efficient treatment options available for depression. (3) Face-to-face CBT could be an option to TAU, but demands more resources. It is also a more rigid control condition which involves a risk of underestimating the effect of I-B. Since this is an early-stage trial of a rather novel format for delivering CBT for depression, where we hope to evaluate whether or not the intervention is effective, we believe TAU is more appropriate. (4)

## 5.3 STUDY SETTING

The study will be conducted at the Child and Adolescent Psychiatry (CAP) Research Centre within Child and Adolescent Mental Health Services (CAMHS) in Stockholm in collaboration with the Department of Clinical Neuroscience at Karolinska Institutet. Participants will formally be considered as patients at the CAP Research center from enrolment to the 3-month follow-up (primary endpoint). All assessments will be administered from a single site, the CAP Research center, at [name] in Stockholm. All counties across Sweden will be able to refer potential participants to the Stockholm site for inclusion in the trial and will be responsible for delivering TAU if participants from their county is randomised to the control group.

## 5.4 POWER ANALYSIS

The sample size has been calculated with the help of KI Biostatistics Core Facility ([www.biostatcore.ki.se](http://www.biostatcore.ki.se)). To estimate power, we conducted a simulation study with 2,000 randomly generated datasets based on the information available from our feasibility study ([name] et al., 2022). In each generated dataset, we estimated a random intercept model with CDRS-R as outcome and time (numeric: post-randomisation months 0, 3 and 6), treatment (three-level categorical with TAU as reference group), and the interaction terms between month and treatment groups as covariates. We assumed a data availability of 85% at 3 months and 77% at 6 months. We tested the null hypothesis that the interaction terms were jointly equal to zero with a 0.05-level Wald test. A sample size of 215 participants yielded 80% power to detect a statistically significant difference of six points in CDRS-R between each experimental group and the TAU group at the 3-month follow-up (6 months post-randomisation). Six points correspond to a medium standardized effect size of 0.5 and align well with our clinical impression of minimal clinically meaningful change. Additionally, findings from the feasibility study ([name] et al., 2022) suggest that an effect of this magnitude can be expected between each of the I-BA groups and TAU.

This power calculation was updated in September 2023. See Appendix 1 for detailed information.

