### 6.3 RANDOMISATION, ENROLMENT AND MASKING

Participants will be randomised at a 1:1:1 ratio to I-BA (guided, self-guided internet-delivered behavioral activation) and a control condition (TAU for depression within CAMHS or pediatric primary care). Randomisation is planned to occur as soon as possible after the diagnostic assessment visit, and never later than 1 month after this visit.

Randomisation will be set up and monitored by the Karolinska Trial Alliance (KTA) using an online randomisation service (ALEA). Randomly varying block sizes of six and nine will be generated using a computer random number generator. We will stratify by two sites, to enable for inclusion of an extra site later on in the trial.

The trial coordinator or co-coordinator will be responsible for enrolment of participants and assigning participants to therapists. Participants will be informed that they will be allocated to one of three arms in the study.

Assessors conducting post- and follow-up assessments will be blind to treatment allocation, until the last follow-up (12FU). The outcome measures are identical for both groups, ensuring that the assessors remain blind. At each follow-up assessment, participants will be reminded by their assessor to not reveal their arm allocation. To measure blinding integrity, all assessors will record whether the participating families inadvertently reveal their group allocation, and subsequently guess each participant's treatment allocation at each assessment point and motivate their choice. The blinding will be broken after the trial's final participant has finished his/her 3-month follow-up assessment (primary endpoint). Blinding of individual participants will be kept for blind assessors until the 12-month follow-up assessment. The trial will end when the trial's final participant has finished his/her 12-month follow-up assessment.

In case of a medical emergency, we will refer participants to appropriate health care. The trial coordinator will be in charge of following up the incident. This whole procedure can be done without unblinding the outcome assessors, so an emergency unblinding system is not required for the trial.

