## 8 STATISTICAL ANALYSIS

**Analysis of trial feasibility:** Descriptive statistics on trial feasibility data, e.g., number of excluded patients and reasons to exclude, participant refusals and causes for refusal (e.g., did not want to be randomised to TAU), withdrawal, and attrition rates, and number of patients who declined to participate and reasons why.

**Summary of baseline data:** All baseline variables will be summarized by randomised group.

**Analysis of acceptability of guided and self-guided I-BA:** Descriptive statistics on treatment satisfaction, treatment credibility and therapist time.

**Analysis of clinical efficacy:** We will follow the CONSORT guidelines in reporting and analyzing our data. The quantitative analyses of continuous measures (primary and secondary outcomes) are conducted according to the “intent-to-treat” principle, including all randomised participants in hierarchical linear mixed-models analysis. Linear mixed models are also an adequate method to handle missing data. Cost data will include resource use costs (e.g., hospital visits, medication and absence from school, caregiver’s absence from work) and cost of I-BA or TAU. Cost differences between guided I-BA, self-guided I-BA and TAU can be calculated, as well as the incremental cost effectiveness ratio (ICER). The ICER is a global estimate of cost-effectiveness and represents the additional cost that is associated with the additional clinical effect in one intervention compared with another.

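### The only model written out leaves the arms' baseline means free, so it forgoes precision that the pre-randomisation CDRS-R could supply at no cost

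*Protocol*

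**What the plan says.** Protocol section 5.4 describes the simulation behind the sample size: "we estimated a random intercept model with CDRS-R as outcome and time (numeric: post-randomisation months 0, 3 and 6", together with "treatment (three-level categorical with TAU as reference group), and the interaction terms between month and treatment groups as covariates". The test is on the interactions alone: "We tested the null hypothesis that the interaction terms were jointly equal to zero with a 0.05-level Wald test". The result is that "A sample size of 215 participants yielded 80% power to detect a statistically significant difference of six points in CDRS-R", with two further inputs: "Six points correspond to a medium standardized effect size of 0.5" and "We assumed a data availability of 85% at 3 months and 77% at 6 months". The within-person correlation is not given, nor are SDs by visit.

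Section 8 commits the efficacy analysis to "including all randomised participants in hierarchical linear mixed-models analysis". It names no fixed effects and does not say how baseline is handled; the summary in section 2 says no more. On randomisation, section 6.3 says: "We will stratify by two sites, to enable for inclusion of an extra site later on in the trial". Site is not among the covariates listed in 5.4.

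Table 2 (section 6.5) schedules CDRS-R at baseline, and section 6.2 (step 8) has the baseline measures completed before randomisation.

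**The concern.** Month 0 is one of the outcome times, so the treatment main effect is the difference between arms at baseline. Because CDRS-R is measured before allocation, that difference is zero in expectation by design. Estimating two such parameters uses up information, and the treatment effect becomes the difference between arms in change from baseline. A model that holds the arms to one month-0 mean, or takes baseline CDRS-R as a covariate, targets the same treatment difference at follow-up with equal or smaller variance and needs no extra data.

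The stake is precision. Recruitment is a stated worry: section 6.1 adds recruitment from a further clinic to improve the inclusion rate, and section 6.6.2 names failure to recruit as a possible reason to stop. Precision from a measurement already taken is useful in such a trial.

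**Working it through.** **Inputs from section 5.4.** N = 215 in three equal arms (215/3 = 71.67 per arm); effect 6 points in each I-BA arm against TAU; availability 100%, 85% and 77% at months 0, 3 and 6; joint Wald test on 2 df at 0.05. SD = 6/0.5 = 12.

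**Assumptions.** SD 12 at every visit; constant within-person correlation rho; monotone missingness (77% with all three visits, 85 - 77 = 8% with months 0 and 3, 15% with month 0 only). Variances come from the generalised least squares information matrix.

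**1. The stated 80%.** For equal arms sharing TAU, the two contrasts have equal variance v and correlation 0.5, so the joint noncentrality is (4/3) x 6^2 / v = 48/v. Power of 80% on 2 df needs 48/v = 9.635, so v = 4.98 (SE 2.23). The model in 5.4 gives this at rho = 0.487 with numeric time, and at 0.489 with categorical time. The 80% is therefore attainable, but it cannot be confirmed independently because rho is not stated.

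**2. Link to change scores, complete data.** With free baseline means, the month-6 contrast has variance 2 x 144 x 2(1 - rho)/71.67. At rho 0.5 this is 4.02, equal to the change-score variance. Baseline adjustment gives 2 x 144 x (1 - rho^2)/71.67 = 3.01. The ratio is (1 + rho)/2 = 0.75. With 85%/77% availability the identity is only approximate: at rho 0.5, v is about 4.85 against 5.09 from within-person change alone, so about 95% of the information is within-person change.

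**3. Effect of a common baseline mean at the calibrated rho.**

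| Time in model | v free | v common | Ratio | Joint power | One pairwise contrast |
|---|---|---|---|---|---|
| Numeric, as in 5.4 | 4.98 | 3.76 | 0.755 | 80% to 90% (48/3.76 = 12.77) | 77% to 87% |
| Categorical | 4.98 | 3.93 | 0.789 | 80% to 89% (48/3.93 = 12.21) | 77% to 86% |

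With the common mean, 80% joint power would need about 162 participants (numeric time) or 170 (categorical).

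**4. Other correlations, SD 12 throughout.**

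| rho | Variance ratio, numeric | Variance ratio, categorical | Joint power, numeric |
|---|---|---|---|
| 0.3 | 0.65 | 0.71 | 67% to 86% |
| 0.5 | 0.76 | 0.79 | 81% to 91% |
| 0.7 | 0.86 | 0.88 | 96% to 98% |

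The saving is thus about 12-35%.

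**5. Narrower baseline spread.** Let k be baseline SD divided by follow-up SD. With complete data the ratio is (1 - rho^2) / [(1 - rho^2) + (k - rho)^2]. At rho 0.5 this is 0.75/(0.75 + 0.25) = 0.75 when k = 1, and 0.75/(0.75 + 0.028) = 0.96 when k = 8/12. It is 1.00 when k = 6/12 = rho. Under the planned missingness, with follow-up SD 12 and categorical time:

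| Baseline SD | Ratio, all correlations 0.5 | Ratio, baseline correlations 0.4 (month 3) and 0.3 (month 6) |
|---|---|---|
| 10 | 0.90 | 0.80 |
| 8 | 0.97 | 0.90 |
| 6 | 1.00 | 0.97 |

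The saving at baseline SD 6-8 is about 0-10%. At SD 8 and rho 0.5 the free-baseline model already has 88% joint power, against 89% with the constraint. The constrained model was not less precise in any scenario.

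**The case against.** The strongest reply is that section 5.4 describes a simulation, not the analysis. A simulation model simpler than the final one is normal, and handling of baseline and of the stratum is ordinary content for a statistical analysis plan that is not shown here. This stands as a limit. A reader might infer that the trial is already committed to the free-baseline analysis, or that the final model will omit site; section 8 says neither. If the analysis does adjust for baseline, then 215 is conservative, not too small. The point survives because 5.4 is the one place where model terms are fixed, and those terms can be improved.

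Second, the model is valid. A reader might infer bias or an inflated type I error; neither follows. Baseline CDRS-R does enter, as an outcome. What goes unused is the knowledge that the expected arm means are equal at month 0.

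Third, the size is uncertain. The 21-25% needs the same SD at baseline as at follow-up and a correlation solved from the very 80% it is meant to explain. Entry is limited to mild or moderate MDD (section 5.5.1), which may well narrow the baseline spread. This stands too: the documents support no guaranteed minimum gain above zero.

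**Conclusion.** The point holds as a free improvement. The model written out in 5.4 is close to a change-score analysis and leaves unused a constraint that randomisation justifies; section 8 does not supply a different model. The cost is efficiency alone. Under constant SD 12 and rho of about 0.49 it amounts to 21-25% of the variance, or joint power of 80% instead of 89-90%. Both conditions are assumptions, since the protocol gives neither the correlation nor a baseline SD. The loss could be as large as 35% at rho 0.3 and close to nothing if the baseline SD is about half the follow-up SD. The missing site term is a minor addition to the same wording change.

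**What to change.** In sections 5.4 and 8, state the primary model as a longitudinal model with one month-0 CDRS-R mean common to the three arms, time, treatment effects at the post-baseline visits, and the randomisation site stratum. Use a covariance that allows the baseline variance to differ from follow-up; a plain random intercept forces them equal and would weight baseline wrongly if entry restriction narrows its spread. An acceptable alternative takes the post-baseline visits as outcomes, with baseline CDRS-R and site as covariates. The common-mean form also keeps participants who have only a baseline value in the model, in line with section 8's inclusion of everyone randomised. Report in 5.4 the correlation and the SDs by visit used in the simulation.

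The cost is a few sentences and a rerun of the simulation, with no new data. It should be done before outcomes are analysed by arm. Section 6.6.2 defers outcome analysis until the primary-endpoint data are complete, and Appendix 1 records the statistician as blinded at the September 2023 update, so the change is clean if that is still the case.

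### The 80% power in section 5.4 belongs to a joint 2-df test but is reported as power for each I-BA arm against TAU

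*Protocol*

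**What the plan says.** Section 5.4 of the Protocol describes a simulation of 2,000 datasets. In each, "we estimated a random intercept model with CDRS-R as outcome and time (numeric: post-randomisation months 0, 3 and 6"), with "treatment (three-level categorical with TAU as reference group), and the interaction terms between month and treatment groups as covariates". The test counted is named: "We tested the null hypothesis that the interaction terms were jointly equal to zero with a 0.05-level Wald test". The next sentences give the assumed data availability and the result: "A sample size of 215 participants yielded 80% power to detect a statistically significant difference of six points in CDRS-R between each experimental group" and TAU at the 3-month follow-up, which is six months after randomisation.

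The primary objective in section 4.1 names guided and self-guided I-BA, each compared with TAU. Research question 1 asks: "Is guided and self-guided I-BA more efficacious than TAU in regard to reduction of depressive symptoms"? Section 8 specifies a hierarchical linear mixed model under intention to treat. It does not name the joint test as the primary test. The superseded calculation in Appendix 1 also rested on a joint null hypothesis.

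**The concern.** A joint test of two interaction terms asks whether the three slopes are all equal. It is non-directional, and one arm alone can cause it to reject. The result sentence instead speaks of a significant difference between each experimental group and TAU, which a reader will take as per-arm power.

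The trial's questions are at arm level. If guided I-BA works and self-guided does not, or the reverse, the practical conclusion differs, yet the joint test cannot tell these cases apart. A reader who relies on 80% for either comparison, or for showing both arms superior, relies on a number that was not computed for that purpose.

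**Working it through.** **Inputs.** From 5.4: alpha 0.05; two interaction terms with TAU as reference, hence 2 df; linear time at months 0, 3 and 6, so six points at month 6 is a slope difference of 1 point per month; N = 215. From 5.1: allocation "at a ratio of 1:1:1 (72 in each group"), i.e. 215/3 = 71.7 per arm. Only steps 1 and 5 also need the SD ("Six points correspond to a medium standardized effect size of 0.5", so 6/0.5 = 12) and the availability ("We assumed a data availability of 85% at 3 months and 77% at 6 months"). The within-person correlation (ICC) is not stated and is varied as an assumption.

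**Step 1: the stated 80%.** Let v be the variance of one arm's estimated slope. Generalised least squares for the random-intercept model, with monotone missingness, gives this joint power:

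| Assumed ICC | Joint power |
|---|---|
| 0.2 | 61% |
| 0.3 | 67% |
| 0.4 | 74% |
| 0.5 | 81% |
| 0.6 | 89% |

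Exactly 80% needs an ICC of about 0.49 (0.48 if missingness is independent across visits). A simulation of 2,000 datasets at ICC 0.5 gave 80.3%. So 80% is plausible for the joint test, but it cannot be confirmed without the ICC.

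**Step 2: joint against pairwise noncentrality.** With equal arms, the two slope contrasts with TAU have covariance matrix v × [[2, 1], [1, 2]]. For true contrasts d1 and d2:

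- joint noncentrality = (2/(3v)) × (d1² − d1·d2 + d2²)
- pairwise noncentrality = d²/(2v)

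If d1 = d2 = d, the joint value is 2d²/(3v). The ratio of pairwise to joint is (1/2)/(2/3) = 0.75. This ratio needs no SD, ICC or dropout figure.

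**Step 3: per-arm power.** The 2-df critical value is 5.99, and 80% power needs noncentrality 9.63. The pairwise value is 0.75 × 9.63 = 7.23, so the expected z is √7.23 = 2.69. Power at two-sided 0.05 is Φ(2.69 − 1.96) = Φ(0.73) = 76.7%.

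**Step 4: decision rules and other effects.** The two z statistics share the TAU arm, so their correlation is 0.5. From the bivariate normal distribution with both means at 2.69:

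| Event | Probability |
|---|---|
| Joint test rejects | 80.0% |
| One given arm significant, no gate | 76.7% |
| One given arm significant, after joint rejection | 72% |
| Both arms significant, no gate | 64.2% |
| Both arms significant, after joint rejection | 63.6% |

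So 80.0 − 63.6 = about 16 points of joint power come from datasets in which at least one comparison is not significant.

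- True effects 6 and 0: 36 − 0 + 0 = 36, the same as 36 − 36 + 36 = 36 for effects 6 and 6. Joint power is again 80%.
- True effects 6 and 3: 36 − 18 + 9 = 27, and 27/36 = 0.75. Joint noncentrality is 7.23 and joint power about 67%.

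**Step 5: other 3-month contrasts.** These depend on assumptions.

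- Model-based difference at month 6 (treatment term plus 6 × slope term), SD 12, ICC 0.487, linear trend: standard error 2.107, so z = 6/2.107 = 2.85 and power = Φ(2.85 − 1.96) = about 81%.
- Endpoint-only comparison with 71.7 × 0.77 = 55.2 per arm and SD 12: about 75% per arm. The 2-df test on the same data has 78%.

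**The case against.** The best defence is that the joint test is disclosed one step before the result. On that reading, six points for each group is just the alternative under which the joint test was simulated, and nothing has been miscalculated. It is also true that, when both arms are six points better, a joint rejection almost never occurs without at least one significant arm-level comparison in favour of I-BA. And the like-for-like gap, 80% against 76.7%, is small beside the simulation's own Monte Carlo margin of about 1.8 points (1.96 × √(0.8 × 0.2/2000)).

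Much of this stands. The 80% is plausible for the test described, and the fault is one of attribution. But the sentence reports power for a significant difference between each group and TAU. Reading it charitably does not turn a joint figure into a per-arm one, and it leaves the comparisons in the primary objective without any stated power. One significant arm is also not the same as a result for each arm.

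Three stronger readings are tempting, and the documents do not support them.

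- A reader might infer that per-arm power must be below 80% whatever is tested. That holds for the slope contrasts only; step 5 gives 75% to 81% depending on the estimator.
- A reader might cite 67% (Bonferroni at 0.025) or a family-wise error near 9% (two ungated tests at 0.05). Both rest on decision rules that the Protocol does not state and that the statistical analysis plan, not shown here, may settle.
- A reader might conclude that 215 participants are too few. The Protocol does not fix the contrast and alpha against which a shortfall could be measured.

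**Conclusion.** The point holds: section 5.4 attaches the power of a joint 2-df test to two arm-level comparisons. For the same month-by-treatment contrasts, a joint power of exactly 80% implies about 77% per arm ungated, 72% per arm when gated by the joint test, and 64% for both arms. These figures assume equal arms, both true effects at six points and a large-sample normal approximation. They do not depend on SD, ICC or dropout. They do not carry over to a month-6 contrast.

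Severity is moderate. The statement should be corrected because the primary objective relies on it, but the closest comparison differs by about 3 points, and neither the design nor the sample size is shown to be wrong.

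**What to change.** In section 5.4:

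1. State that 80% is the power of the joint test at N = 215.
2. Add power for the same month-by-treatment contrasts: about 77% per arm ungated, about 72% per arm after a significant joint test, about 64% for both arms. Alternatively, re-run the simulation for whichever 3-month contrast and alpha the analysis will use, and report the SD and ICC assumed.
3. State that joint significance alone supports no claim about either arm.

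If the joint test is to be the primary test, say so. The two comparisons with TAU can then each be tested at 0.05 only after joint rejection. With two hypotheses this controls the family-wise error without a further alpha split, provided that the joint and pairwise tests concern the same parameters.

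The cost is one paragraph and a slightly less favourable stated power. No extra patients are needed.
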